### Data management {19}

Utilization data from the electronic medical record systems of the two health systems will initially be extracted in aggregate by information technology staff. These data will be transmitted to the study data analyst in an encrypted format.

The project coordinator will transmit to the data analyst double-entered and corrected datafiles containing data from standardized patient follow-up encounters. The data analyst will have access to the REDCap database containing clinician survey responses.

With the direction of the principal investigator and the study statistician, the data analyst will develop analytic variables, link the datasets, and develop a final, blinded analytic dataset. The analyst will transmit this dataset to the study statistician using encrypted file transfer protocols.

All datasets will be stored on password-protected computers behind University-based firewalls.

### Confidentiality {27}

The project coordinator will maintain data on potential and enrolled clinicians in password-protected computers in research offices at the UCD Medical Center. Similar files will be maintained by the study coordinator at the Sutter Institute for Medical Research. Both institutions maintain the highest level of cybersecurity with computers protected behind certified firewalls. All participants will be identified by unique study identification numbers that will be included in a password-protected file maintained by the study coordinators at each site. All other research datafiles will contain only the study identification number, reducing the risk of breach of confidentiality of individual participating clinicians. Research coordinators will access the identifying information only for essential trial activities, such as communication with participating clinicians about upcoming standardized patient visits, compensating clinicians for study visits, collection of pre- and post-trial surveys, and study closure.

### Plans for collection, laboratory evaluation, and storage of biological specimens for genetic or molecular analysis in this trial/future use {33}

Not applicable.

Secondary outcomes include (1) clinician implementation of specific watchful waiting techniques based on coded audiotapes and standardized patient ratings (likely a summary scale), (2) clinician self-report of the use of watchful waiting with actual patients (an ordinal measure), and (3) actual patient satisfaction with their recent experience with clinicians (likely a *z*-score based on seven survey items). When there is a single secondary outcome per clinician, we will analyze for intervention effects using ordinal or logistic regression as indicated by the response variable within a GLMM model with random intercepts for the units of randomization. For analyses of patient experience, we will also use generalized linear mixed models (GLMM) with similar random effects specified as above and with the distribution and link functions tailored to the outcome variable (Gaussian for the *z*-score outcome) [27, 28].

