## Trial design {8}

This will be a parallel group randomized trial with primary care clinicians randomized to intervention and control arms. We considered cluster randomization at the clinic level which would reduce risk that intervention clinicians will discuss their experiences with the watchful waiting messages with clinicians randomized to the control arm in the same clinic, potentially introducing contamination of that arm via their social influence on peers. However, recruitment challenges in the context of the COVID-19 pandemic made it difficult to recruit entire clinic staffs to the study simultaneously, which made a clinic-level cluster randomization scheme infeasible. We will therefore randomize clinicians overall 1:1 to intervention and control groups, which allow rolling enrollment and initiation of trial procedures in the context of ongoing pandemic mitigation. The trial is designed as a superiority trial, testing whether the intervention is superior to the control condition in reducing rates of low-value spinal imaging.

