The post-intervention rate of cervical spinal imaging among adults adjusted for baseline rate (to examine the potential for the intervention effects to generalize beyond the management of low back pain (objective 3)). We will compute this analogously to the rate of lumbar spinal imaging but only among patients with “neck pain” diagnoses in the primary position using ICD-9 and ICD-10 codes [23, 24].The rate of overall diagnostic testing among adult patients adjusted for baseline. For these analyses, we will identify counts of diagnostic tests ordered during primary care visits participating clinicians during the 24-month period prior to their first SPI visits and from the date of their final SPI visits through up to 18 months, consistent with our pilot trial [21]. Specifically, we will include visit-level counts of the following diagnostic test categories: hematology and chemistry, urine and body fluid analyses, microbiology, imaging tests (subcategorized as non-spine plain x-ray or sonography, spinal x-ray, non-spine MRI or CT, neuroimaging), electrocardiography, other cardiac tests, and miscellaneous tests (e.g., nuclear medicine). We will exclude tests performed for screening or prevention (e.g., lipid or diabetes mellitus tests, bilateral screening mammograms). Both UC Davis and Sutter utilize the same EMR system (Epic), and so we expect to be able to harmonize patient and visit EMR data extracted from the two systems. The analysts compiling these data will be blinded to the study arm.The post-intervention rate of test *ordering* which is distinct from test *completion*. These outcomes will be computed similarly as the test completion outcomes specified above, but we will use a signifier in the electronic medical record that a given test was ordered by the clinician. Because not all ordered tests are completed by patients, we assess test ordering as a secondary outcome.Approximately 7–9 months after clinician enrolment (and after all intervention visits are completed among intervention physicians), intervention and control physicians will receive a visit by a single non-instructor SP portraying a patient with acute low back pain. Using SP observations and audio-recordings of these visits, we will ascertain as a *secondary outcome* the extent to which clinicians implemented various steps of the model. We will use iterative systematic content analysis of transcripts from audio-recorded visits to quantify how frequently clinicians engaged in the specific steps emphasized in the intervention, as well as the overall extent to which clinicians implemented watchful waiting. To guide coding, we will develop a manual to guide trained research assistants in coding transcriptions while simultaneously listening to audio-recorded visits. As the first step in the model addresses non-verbal communication, we will also incorporate standardized patient ratings on non-verbal communication. Coders will be blinded to clinician allocation. To the extent possible, we will blind SPs to the intervention group, but given the small number of total SPs, some SPs may revisit clinics where they previously performed the role of intervention SPIs, thereby making SP blinding difficult if not impossible without training and hiring entirely new SPs for the assessment phase. Inter-observer agreement for coding targeted behaviors will be assessed using Cohen’s kappa, and disagreements will be resolved by consensus or by review of the audio-recording by a third party. We have successfully used this process to assess physician-patient interaction in other studies [19, 21]. Ultimately, this process will generate a summary scale expressing the extent to which clinicians engaged in intervention steps during SP visits.Six months after final SPI visits, we will survey randomized clinicians regarding the use of watchful waiting when actual back pain patients request low-value spinal imaging. We will also survey physicians regarding the use of watchful waiting for neck pain, other regional musculoskeletal pain syndromes (e.g., shoulder and knee pain), and in other contexts (e.g., when patients request antibiotics). For intervention clinicians, the survey will also inquire regarding clinicians’ views on the quality, acceptability, and utility of the SPI training. Clinician self-reported use of watchful waiting during the follow-up period will constitute a *secondary outcome* of the trial.To address concerns that a watchful waiting strategy might undermine patient trust and confidence in physicians, we will assess as a *secondary outcome* for potential adverse impacts of the intervention on patient experience. To develop this measure, we will link study physicians to pre- and post-intervention patient experience data collected by the health systems as part of routine care. We have confirmed the feasibility of such linkage with UC Davis executives and are exploring this possibility within the Sutter system. These measures include visit-level Consumer Assessment of Healthcare Providers and Systems (CAHPS) results [25], which we will use to develop pre- and post-intervention summary measures of patient experience. Analyses will assess for adjusted differences in post-intervention patient experience measures among intervention physicians as compared to control physicians, after adjustment for baseline patient experience.

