## Assignment of interventions: blinding

### Who will be blinded {17a}

It will not be feasible to blind study clinicians to intervention and control assignments. Although we will not explicitly inform control clinicians of their assignment, these clinicians may infer their assignment as they will receive no standardized patient instructor visits.

We will blind research assistants hired to code transcripts of recorded follow-up visits with standardized patients. We will attempt to recruit standardized patients solely for the 9-month evaluation visits so that these standardized patients, who will rate clinicians on non-verbal communication, can be blinded to intervention vs. control arm. To blind coders, the project coordinator will assign a study identification number to each transcript prior to distribution to coders. The coordinator will also review the transcript for any language that may divulge the intervention assignment and will delete this from the transcript. To blind standardized patients, the project coordinator will not divulge to the standardized patients the intervention assignment of clinicians.

We will blind the study statistician to intervention assignments. The data analysts who extract diagnostic testing data from EMR databases will be blinded to intervention status. These data will be securely transferred to a project data analyst who will construct the final analytic dataset. The project data analyst will not be blinded to allocation assignments and will assign an unlabeled indicator variable to each clinic, thereby masking the intervention assignment. The final analytic dataset will be transmitted to the study statistician, and the data analyst will only divulge allocations after the study statistician has completed planned primary and secondary analyses.

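### The model for the follow-up standardized-patient visit has no term for which standardized patient (SP) made the visit, and nothing balances the small pool of SPs across arms

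*Protocol article*

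**What the plan says.** All places are in the protocol article.

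- **The visit.** Outcomes {12}: some 7 to 9 months after enrolment, "intervention and control physicians will receive a visit by a single non-instructor SP portraying a patient with acute low back pain". So there is one such visit per clinician.
- **The SP as rater.** The same section says that "we will also incorporate standardized patient ratings on non-verbal communication". Who will be blinded {17a} confirms it, speaking of "these standardized patients, who will rate clinicians on non-verbal communication". The remaining steps of the communication model are coded from transcripts and recordings by blinded coders.
- **The pool.** Outcomes {12}: "given the small number of total SPs, some SPs may revisit clinics where they previously performed the role of intervention SPIs". Section {17a} says only that recruitment of separate evaluation SPs will be attempted. No number of SPs is given.
- **The model.** Statistical methods {20a}: for one value per clinician, ordinal or logistic regression "within a GLMM model with random intercepts for the units of randomization". The same section lets baseline clinician characteristics enter each model as fixed effects where they improve precision.
- **The unit of randomization.** Trial design {8}: "We will therefore randomize clinicians overall 1:1 to intervention and control groups". Section {20a}, however, mentions clinicians nested within units of randomization, which reads as if the unit were the clinic.

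No section says how follow-up SPs are allotted to clinicians.

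**The concern.** The SP shapes the score in two ways: by how the patient's worries and imaging requests are played, and by how strictly non-verbal behaviour is marked. Scores from visits made by the same SP therefore share a component. The model as stated does not represent it. If the intercept is per clinician, there is one observation per intercept and it cannot capture anything SPs have in common. If it is per clinic, it picks up SP differences only so far as SPs happen to work by clinic. Double coding and kappa deal with disagreement between coders, not with differences between SPs.

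At stake is the only directly observed evidence that training changed communication. With even SP assignment the cost is some precision. With uneven assignment, differences between SPs enter the arm comparison. Clinicians in both arms are visited, so the trial will already hold the data needed to remove the SP component.

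**Working it through.** **The plan's own figure.** Sample size {14} gives 80.1% power, for the primary imaging outcome only. With 24 clinicians per arm, 57 pre and 35 post visits each, 25% versus 18%, on the logit scale:

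- difference = |logit 0.18 − logit 0.25| = 0.418
- variance = 2/(24·57·0.1875) + 1/(24·35·0.1875) + 1/(24·35·0.1476) = 0.0222, so SE = 0.149
- power = Φ(0.418/0.149 − 1.96) = 80.0%

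The figure reproduces, and the present point does not touch it. No power is stated for the SP-visit outcome. With 24 per arm the effect detectable at 80% power is (1.960 + 0.842)·√(2/24) = 0.81 SD.

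**Inputs for the SP-visit outcome.** From the documents: 48 retained clinicians (24 per arm), one visit each, two-sided 5%. Assumed, because the documents are silent: number of SPs (2, 3 or 4), SP share *s* of outcome variance (5 to 30%), the split of SPs over arms, and a Gaussian score with total variance 1.

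**Case 1: three SPs, balanced (8 clinicians per SP per arm).** Without an SP term the expected within-arm variance is (1 − *s*) + *s*·16/23; with it, 1 − *s*. The SE ratio is √[(1 − *s*)/(1 − 7*s*/23)].

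| SP share | SE ratio (formula) | Mean SE without / with term (simulation) | Power at 0.83 SD without / with |
|---|---|---|---|
| 0% | 1.00 | 0.286 / 0.286 | 80% / 80% |
| 10% | 0.963 | 0.281 / 0.271 | 83% / 84% |
| 20% | 0.923 | 0.279 / 0.258 | 83% / 87% |
| 30% | 0.878 | 0.273 / 0.241 | 87% / 92% |

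The SE falls by about 4, 8 and 12%, and power rises by 1, 4 and 5 points. A separate simulation with 2 or 4 SPs, balanced or randomly spread, shares of 5 to 20% and a 0.81 SD effect gave power changes of about −1 to +4 points. Type I error without the term was 3.4 to 5.6%.

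**Case 2: two SPs, split 2:1 in opposite directions by arm.** The arm difference contains (2/3 − 1/3) times the SP difference, whose variance is 2*s*.

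- true variance of the estimate = (1/9)·2*s* + (1 − *s*)/12
- expected reported variance without the term = [(1 − *s*) + (2/9)·2*s*·24/23]/12

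For *s* = 20%: √0.1111 = 0.333 true against √0.0744 = 0.273 reported, a ratio of 1.22. The t test with 46 df then rejects at |t| > 2.013/1.22 = 1.65, or about 10.6%. The same steps give about 6.3% at *s* = 5% and 7.6% at 10%. Simulation gave 6.6%, 7.9% and 9.1% for shares of 5, 10 and 20%. With four SPs at 2:1 it gave 4.9 to 6.3%.

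**Case 3: split 5:1.** Simulated type I error without the term is 11 to 27% with two SPs and 8 to 15% with four.

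**With the SP term,** type I error stays at 4.4 to 5.8% throughout.

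**Price of the term under imbalance.** The arm variance is multiplied by 1/(1 − *q*²), where *q* is the difference between arms in one SP's share of visits. At 2:1, *q* = 1/3 and the factor is 1.125; if SPs do not differ, power at 0.81 SD drops from about 78% to 73%. At 5:1, *q* = 2/3 and the factor is 1.8; simulated power with the term is 55 to 64%.

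**The case against.** **This is detail for an analysis plan that is not shown.** A rater covariate and a visit schedule often are. The text is also provisional: the scale is only described as likely. But section {20a} does name the random effect and the class of covariates for these outcomes, and SP identity belongs to neither. The point stands as an improvement to a stated model, not as an error in it.

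**A reader might infer that the arm effect will be biased.** The documents do not support that. Bias needs SPs to be distributed differently over the arms. Rolling enrolment and possible reuse of instructors make this conceivable, but nothing states it. A moderate example is mild: two SPs 0.5 SD apart, one making 70% of visits in one arm and 50% in the other, shift the estimate by 0.20 × 0.5 = 0.10 SD. That is 0.35 of a 0.286 standard error, and type I error is then about 6.4%. The large figures need a 5:1 split.

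**A reader might infer that SPs score the whole outcome.** They rate only non-verbal behaviour; the rest is coded twice by blinded coders. Portrayal can still affect what is there to be coded.

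**A reader might infer that the random intercept is useless and should be replaced.** Given the wording about clinicians nested within units of randomization, the intercept may be at clinic level. Sample size {14} assumes a within-clinic correlation, so deleting the term is not safe.

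**One SP for the whole trial?** The phrase on a single SP could be read so, and SP variation would then vanish. The plurals in {12} and {17a} point to several SPs.

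**The calculations use a Gaussian score,** whereas the article names ordinal or logistic regression. That limitation stands; the sizes are indicative.

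**Conclusion.** The point holds in limited form. A few SPs generate the follow-up visit outcome and rate part of it, the stated model has no term for them, and no rule balances them over arms. With balanced SPs the loss is modest: about 4 to 12% of the standard error, or 1 to 5 power points, assuming three SPs and a 10 to 30% share. With a 2:1 imbalance, two SPs and a 5 to 20% share, type I error is about 6 to 10%; only more extreme splits take it well beyond that. The number of SPs, their variance share and their split over arms are all assumptions. The finding concerns one secondary outcome, in a study that calls itself developmental and does not adjust for multiplicity. It does not affect the primary imaging outcome or its stated power. It is worth doing because it is cheap, not because the trial's conclusion depends on it.

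**What to change.** 1. **Outcomes {12}:** have the study coordinator, who already knows the allocations, assign follow-up SPs from a list balanced over the two arms within each randomization stratum, without revealing arm to the SPs. Settle this before follow-up visits start, because adjustment alone does not restore the power lost to a severe imbalance.
2. **Statistical methods {20a}:** for the communication outcome only, add the identity of the follow-up SP as a fixed factor. Keep any clinic-level random intercept alongside it. A clinician-level intercept is redundant with one observation per clinician. The text should say which level the units of randomization denote here.

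Cost: a scheduling list and 1 to 3 degrees of freedom (2 to 4 SPs) out of about 46, with no extra visits, staff or data. The downside is some loss of power if assignment ends up unbalanced and SPs turn out not to differ, about 78% to 73% at a 2:1 split. The balanced list is meant to prevent this.

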### Interim analyses {21b}

No interim analyses will be performed.

### Methods for additional analyses (e.g., subgroup analyses) {20b}

Although our sample of urgent care clinics will be small (likely two), we will plan to conduct analyses of the primary outcome with clinicians stratified as primary care vs. urgent care. We will also conduct a subgroup analyses with clinicians stratified by years of experience (e.g., above or below the median years of experience for the clinician sample) and physicians vs. nurse practitioners/physician assistants. If many intervention visits are delivered by video, we will assess whether the modality of intervention delivery (in-person vs. video) modified intervention efficacy.

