### Intervention description {11a}

Clinicians randomized to the control group will receive no intervention during the trial period.

Clinicians randomized to the intervention group will receive three visits over a 3- to 6-month period with an SPI scheduled during normal clinic hours for 20-min in-person office visits. (Due to the COVID-19 pandemic, clinicians may opt to have the second or third SPI visits as video visits, although we will require that the initial SPI visit be conducted in-person.) Clinicians will be aware that they are scheduled to see a standardized patient, and the SPI will begin the visit by reminding the clinician that they are an SP and orienting the clinician to the overall visit plan. During each visit, SPIs will spend 10–12 min portraying a patient with acute back pain based on pre-specified role profiles. During this time, SPIs will assess clinicians’ performance on a three-step intervention model for communicating a watchful waiting message regarding spinal imaging that is based on psychological theory [15–17], extant literature and preliminary studies [18–22], key informant interviews with clinicians, and focus groups with patients (Table 1). We consider the model to be preliminary at this stage, as we may modify content based on additional key informant interviews or our experience during SPI training and intervention pilot testing.

**Table 1 Tab1:** Watchful Waiting to Avoid Inappropriate Testing (WAIT): intervention model with key skills and criteria for fulfillment

Step	Key skills	Criteria for fulfillment with examples (to guide intervention content and coding)
1. Set the stage for deferred imaging by building trust	1. Demonstrate openness and interest 2. Avoid interruptions 3. Identify the patient’s motivating concern or expectations	1. Non-verbal openness and engagement • Sits, orients toward the patient • Maintains open body position, leans in • Frequent, attentive eye contact • Engaged facial expressions or gestures (e.g., nodding) 2. Clinician does not interrupt early on. Allows patient to “tell their story” without cutting them off. 3. Clinician probes or asks for more information when patient signals a major underlying or motivating concern or expectations: “It sounds like you are worried that you seriously injured your back. Is that right?” or “You seem to be concerned that you need an MRI. Can you tell me more about that?”

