## Assignment of interventions: allocation

### Sequence generation {16a}

We will stratify randomization by health system (UC Davis vs. Sutter) and primary vs. urgent care (within the Sutter system only). We will then use block randomization (in blocks of four clinicians) to ensure balance by overall, by health system, and by primary vs. urgent care.

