The primary outcome of the trial is the spinal imaging rate among actual back pain seen by study clinics after the intervention. To identify this outcome, we will abstract test ordering and completion data from the electronic medical records of two health systems. Secondary utilization outcomes will also derive from electronic medical record data. While each system uses the same electronic record, we anticipate some logistical challenges in ensuring abstraction of equivalent data in each system. We are developing relationships with information technology leaders at each site, and as data extraction begins, we will hold regular meetings with information technology staff at the two sites to engender a team approach to the data extraction. Analysts at the two sites will be encouraged to communicate regularly outside of team meetings and to work simultaneously and collaboratively in the extraction of required data elements.

The COVID-19 pandemic poses some operational challenges. While we anticipate that clinicians will be willing to participate and to receive SPI visits in-person, some clinicians may opt to have some of the SPI visits via video technology. We have explored the feasibility of implementing video visit technology at each site and do not anticipate difficulties. However, we have some concerns that clinicians may be less responsive to instructor feedback if delivered via video as compared to in-person. We will therefore require that at least the initial SPI visit be conducted in-person, and if many SPI visits are delivered using video technology, we will conduct secondary subgroup analyses to assess whether modality modifies intervention efficacy. The pandemic will also necessitate additional training of SPs in hygiene and social distancing precautions to minimize SPI and clinician infection risk during SP visits.

If the intervention reduces the rate of spinal imaging among actual back pain patients (the primary outcome), then SP-based training within simulated office visits may be a feasible means of reducing the overuse of this diagnostic test in clinical practice. Compared to other quality improvement interventions, the intervention is efficient with clinician time (60 min over 3 visits), and clinicians have been receptive to SP interventions during routine office hours, as they require no out-of-office time commitment. Clinicians receiving prior SPI interventions have also found to be fun, instructive, and relevant to practice [21, 26].

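### Video or in-person delivery is chosen after randomization and does not exist for controls, so it cannot be tested as a modifier of the intervention effect

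*Protocol article*

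**What the plan says.** Under Methods for additional analyses {20b}, the Protocol article lists clinician subgroups by care setting, years of experience and profession, and then adds that, on condition that video is used for many of the visits, "we will assess whether the modality of intervention delivery (in-person vs. video) modified intervention efficacy". The Discussion voices a worry that clinicians may take less from feedback given by video, and says that if video is used widely "we will conduct secondary subgroup analyses to assess whether modality modifies intervention efficacy".

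Intervention description {11a} settles how modality arises. In the intervention arm, "clinicians may opt to have the second or third SPI visits as video visits", while "we will require that the initial SPI visit be conducted in-person". For the other arm, "Clinicians randomized to the control group will receive no intervention during the trial period".

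Trial design {8} fixes the ratio: "We will therefore randomize clinicians overall 1:1 to intervention and control groups". Sequence generation {16a} stratifies by health system and, within Sutter, by primary versus urgent care. Modality is neither randomized nor a stratification factor.

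**The concern.** A treatment effect is modified by a variable when the intervention-versus-control difference is larger at one level of that variable than at another. Each level must therefore contain both arms. Modality has no levels among controls, and among intervention clinicians it is a choice made after allocation. The article nevertheless places it beside three baseline subgroups and describes the result in the same terms.

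At stake is the reading of a practical question that the authors raise themselves: does the training lose force when later visits move to video? As worded, the plan invites a conclusion about video from a difference that may reflect who chose it. Enrolment is rolling and takes place during a pandemic, so the choice could plausibly follow calendar time, site or setting, and these may relate to changes in imaging.

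**Working it through.** **1. The planned subgroups side by side**

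| Variable | Fixed before allocation? | Defined in both arms? |
|---|---|---|
| Primary vs urgent care | yes | yes |
| Years of experience | yes | yes |
| Physician vs NP/PA | yes | yes |
| Modality of visits 2-3 | no, clinician's choice | no, intervention arm only |

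Modality is also not a clean two-level variable. Visit 1 is always in person, and visits 2 and 3 can each be either, which gives 2 × 2 = 4 patterns. No clinician is trained wholly by video.

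**2. What can be computed**

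Let V, I and C be the mean pre-post changes in imaging among video choosers, in-person choosers and controls. Comparing each chooser group with all controls and taking the difference gives (V − C) − (I − C) = V − I. The controls cancel. Either route leads to the same non-randomized contrast within the intervention arm.

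**3. The plan's own power figure (Sample size {14})**

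Inputs: 48 clinicians, so 24 per arm; 57 pre and 35 post visits each; rates of 25% and 18%; two-sided 5%. Visits per arm: 24 × 57 = 1,368 pre and 24 × 35 = 840 post.
- Effect on the log-odds scale: ln(0.25/0.75) − ln(0.18/0.82) = 0.418.
- SE = √[2/(1,368 × 0.1875) + 1/(840 × 0.1875) + 1/(840 × 0.1476)] = 0.149.
- Power = Φ(0.418/0.149 − 1.96) = 80.0%, against the stated 80.1%. The inputs are reproduced and are not in dispute.

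**4. Precision of the modality contrast**

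With 12 video and 12 in-person choosers (an assumed split), on the risk scale:
- SE = √[2 × 0.1476/(12 × 35) + 2 × 0.1875/(12 × 57)] = 0.0354.
- Smallest difference detectable with 80% power: (1.96 + 0.84) × 0.0354 = 9.9 points.
- Power for a 7-point difference: Φ(0.07/0.0354 − 1.96) = 51%.
- With a 16/8 split this falls to 46%, and with 18/6 to 40%.

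These figures allow for binomial variation only, so they are on the favourable side.

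**5. Size of a possible selection effect**

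This is a simulation with assumed inputs: 24 intervention clinicians split 12/12, no true modality effect, between-clinician SD of 0.4 in baseline logit, a t test on pre-post change, and 4,000 runs per row. Responsiveness is a clinician's own departure from the average effect on the logit scale. An SD of 0.42 is about as large as the average effect itself.

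| How video is chosen | Spurious difference (points) | False positives |
|---|---|---|
| Unrelated to response, SD 0 | 0.0 | 5.8% |
| Unrelated to response, SD 0.42 | 0.0 | 5.3% |
| Correlated 0.5 with baseline level only | −1.1 | 5.3% |
| Correlated 0.3 / 0.5 / 0.7 with response, SD 0.2 | 1.4 / 2.4 / 3.3 | 6% / 9% / 15% |
| Correlated 0.3 / 0.5 / 0.7 with response, SD 0.42 | 2.9 / 4.7 / 6.7 | 10% / 19% / 33% |

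The mildest correlated case (6%) is hardly distinguishable from no selection. The strongest nearly equals the 7-point design effect.

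**6. Selection through care setting**

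Assume that modality does nothing and that the true effect is −4 points in primary care and −10 in urgent care. If all video choosers are in primary care and in-person choosers are half urgent care, the in-person group shows 0.5 × (−4) + 0.5 × (−10) = −7 and the video group −4, a gap of 3 points. (With equal groups, a quarter of the arm is urgent care, so the arm average is 0.75 × (−4) + 0.25 × (−10) = −5.5.) Within primary care both groups show −4 and the gap is 0, so adjustment for stratum removes this particular bias. It would not remove selection on unmeasured responsiveness.

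**The case against.** The strongest reply is that the article says only that modification will be assessed. It specifies no arm-by-modality interaction, no comparison with all controls and no unadjusted model. The analysis is conditional and secondary, and a condensed article may leave comparison group and covariates to an analysis plan that is not shown. That is fair as far as model detail goes, and the absence of such detail is not the point here. But no analysis plan can give controls a modality or make the choice random. The stated inference, modification of efficacy listed as a subgroup analysis, is wrong whatever model is used.

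A second reply is that differencing before and after removes stable differences between choosers. It largely does, as the third row of the simulation shows. A reader might infer that the analysis is bound to report self-selection as effect modification. The documents do not support that: bias needs the choice to be related to response or to time trend, and the article gives no information on either.

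A third reply is that the study is described as developmental and that all results are to be published together to aid careful reading. This lowers the stakes but does not correct the label.

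A reader might also think that asking all clinicians before allocation which modality they would prefer, and testing arm by preference, would rescue the analysis. That variable would be a valid baseline subgroup, but preference is self-selected too. In the care-setting example it reproduces the same −4 against −7 with no modality effect. It shows whether effects differ by type of clinician, not whether delivery mode matters.

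**Conclusion.** The point holds as a fault of inference in one secondary, conditional analysis. Modality is chosen after randomization and exists in one arm only, so it cannot be tested as treatment-effect modification. This follows from the article's own description and needs no assumption.

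The size of any bias is not known. Under the assumed inputs it runs from none (choice unrelated to response) to 6.7 points with a 33% false-positive rate. A null result would be equally weak, given about 51% power for a 7-point difference at an even split.

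A reader might infer that the trial's main finding is at risk. It is not: the primary comparison is of randomized arms and does not use modality.

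**What to change.** In Methods for additional analyses {20b} and in the Discussion, take modality out of the subgroup analyses and drop the wording that it modified efficacy. Plan instead an exploratory comparison, labelled non-randomized and confined to the intervention arm, of pre-post change in imaging by modality of visits 2 and 3. Define the modality variable beforehand (for example, any video visit versus none). Adjust for randomization stratum (health system, and primary versus urgent care) and for the clinician's baseline imaging rate. State that no causal conclusion about video delivery will be drawn.

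The cost is a change of wording, with no effect on trial conduct. The price is a weaker claim from a small comparison of about 24 clinicians (48/2), in which adjustment covers measured predictors of the choice only.
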